# Remote monitoring of rheumatoid arthritis (REMORA): study protocol for a stepped wedge cluster randomized trial and process evaluation of an integrated symptom tracking intervention

**DOI:** 10.1186/s13063-024-08497-9

**Published:** 2024-10-15

**Keywords:** Mobile health, Patient-generated health data, Randomized controlled trial, Rheumatology, Signs and symptoms, Telemedicine

## Abstract

**Background:**

Management of rheumatoid arthritis (RA) relies on symptoms reported by patients during infrequent outpatient clinic visits. These reports are often incomplete and inaccurate due to poor recall, leading to suboptimal treatment decisions and outcomes. Asking people to track symptoms in-between visits and integrating the data into clinical pathways may improve this. However, knowledge on how to implement this into practice and its impact on services and outcomes remains scarce in RA. Therefore, we evaluate the comparative effectiveness and cost-effectiveness of integrated symptom tracking in people with RA over and above usual care, while generating insights on factors for successful implementation.

**Methods:**

In this superiority stepped wedge cluster-randomized controlled trial with continuous recruitment short exposure design, 16 rheumatology outpatient departments (clusters) recruit a total of 732 people with active RA. They initially offer clinic visits according to standard of care before switching in pairs to visits with integrated symptom tracking. Clusters switch in randomized order every 3 weeks. Integrated symptom tracking consists of (1) a mobile app for patients to track their symptoms daily and other RA aspects weekly/monthly, and (2) an interactive dashboard visualizing the app data, which healthcare professionals access from their electronic health record system. Clinic visits happen according to usual practice, with tracked symptom data only reviewed during visits. Our primary outcome is a difference in marginal mean disease activity score at 12 ± 3 months between standard of care and integrated symptom tracking, after accounting for baseline values, cluster, and other covariates. Secondary outcomes include patient-reported disease activity, quality of life and quality-adjusted life-years, medication/resource use, consultation and decision-making experience, self-management, and illness perception. We also conduct interviews and observations as part of a parallel process evaluation to gather information on implementation.

**Discussion:**

Our trial will generate high-quality evidence of comparative and cost-effectiveness of integrated symptom tracking compared to standard of care in people with RA, with our process evaluation delivering knowledge on successful implementation. This optimizes the chances of integrated symptom tracking being adopted more widely if we find it is (cost-) effective.

**Trial registration:**

Registered 4-Jun-2024 on https://www.isrctn.com/, ISRCTN51539448.

**Trial open science framework repository:**

https://osf.io/sj9ha/.

**Supplementary Information:**

The online version contains supplementary material available at 10.1186/s13063-024-08497-9.

## Introduction

One in three people in the United Kingdom (UK) and in other countries live with at least one long-term condition, collectively accounting for a significant part of all healthcare expenditure [1–3]. One such long-term condition is rheumatoid arthritis (RA): a chronic immune-mediated inflammatory disease that causes joint pain, swelling, stiffness and associated disability. RA affects many people worldwide [4], including just below 1% of the UK population [5].

Long-term conditions, such as RA, are commonly managed jointly by general practitioners and hospital specialists, where the latter decide on treatment based on infrequent outpatient clinic visits that happen once every 3–12 months [6, 7]. During these visits, assessment of disease activity relies on patient descriptions of symptoms and flares. However, answering the hospital specialist’s question ‘How have you been since your last visit?’ is challenging for patients because it asks them to recall flares and summarize fluctuating symptoms over an extended period [8]. This results in incomplete and inaccurate information [9, 10], which may lead to suboptimal treatment decisions and ultimately to worse outcomes [11].

Asking people to track their symptoms between clinic visits has the potential to provide a clearer picture of disease. In the context of RA trials, daily symptom tracking confirmed its benefits of reducing recall error and enabling more robust evaluation of treatment response [12]. Information on tracked symptoms, if made available during visits, could inform better shared decision-making [13, 14]. For example, by revealing flares that would otherwise remain undetected, or by providing a completer and more accurate picture of response to changes in medication [15, 16]. Better decision-making may, in turn, lead to better long-term outcomes, as well as making patients feel more empowered and improving their satisfaction with care [17]. Lastly, symptom tracking may enhance people’s confidence and ability to self-manage their condition [13, 18], which could reduce burden on healthcare services [19].

The interest in integrating electronic patient-generated health data, such as tracked symptoms, into clinical pathways is growing, with national healthcare strategies recognizing its potential to transform outpatient services and make them more person-centred [20–22]. To date, however, evidence of its impact on services and outcomes and knowledge on factors affecting its successful implementation remain scarce in RA and other musculoskeletal diseases [23–25]. Previous studies in RA were not randomized, were conducted in a single centre, recruited a small and/or highly selected sample, used lower-tech interventions (e.g. SMS text messages), collected patient-generated health data infrequently (e.g. monthly), did not integrate it into electronic health records and/or did not assess the impact on clinical outcomes or patient experience [25–31].

After completing a successful proof-of-concept study [15] and mixed-methods feasibility trial [32], we are therefore undertaking a stepped wedge cluster randomized controlled trial called REmote MOnitoring in Rheumatoid Arthritis 2 (REMORA2). It evaluates the comparative effectiveness and cost-effectiveness of integrated symptom tracking in people living with RA over and above usual care, while also generating insights into its impact on shared decision-making and into factors that influence its successful implementation in clinical practice. The current protocol details our plans for the REMORA2 trial and follows the Standard Protocol Items: Recommendations for Interventional Trials (SPIRIT) outcomes 2022 extension reporting guidance [33] (see Additional file 1 for completed checklist).

## Objectives

Our stepped wedge cluster randomized controlled trial aims to evaluate if integrating frequent patient-reported symptom tracking into clinical pathways and systems improves care and outcomes for people living with long-term conditions, using RA as an exemplar. A parallel process evaluation [34] aims to generate knowledge on how to successfully implement electronic patient-generated health data into clinical practice, including the necessary change of workflows and patients’ and healthcare professionals’ behaviours.

### Primary objective

The primary objective of the trial (objective 1) is to evaluate the effect of clinic visits with integrated symptom tracking compared with standard of care on disease activity in people living with RA attending rheumatology consultations in outpatient hospital care settings at 12 months’ follow-up.

### Secondary objectives

The secondary objectives of the trial are to:2.Evaluate the effect of clinic visits with integrated symptom tracking, compared with standard of care, on:Secondary quantitative indicators of disease activity and impact at 12 months’ follow-up.Shared decision-making, self-management and people’s consultation experience, using mixed methods.3.Identify barriers to behaviour change, intervention uptake, and wider implementation into clinical practice, and ways to address these barriers.4.Evaluate the incremental cost-effectiveness of integrated symptom tracking in RA compared with standard of care.5.Explore possible mechanisms that may explain any observed improvement in disease activity (or lack thereof) in relation to integrated symptom tracking, using mixed methods.

### Tertiary objectives

Depending on available time and resources within the study team, we may address tertiary objectives by analysing data collected for addressing the primary and secondary objectives. Potential examples include examining the representativeness and diversity of study participants compared to the wider RA population, exploring longitudinal trajectories of symptoms in response to treatment, and identifying factors associated with patients’ engagement with integrated symptom tracking. A final set of tertiary objectives will be determined at a later stage and will therefore not be described further in this protocol.

## Methods

### Trial design

This is a non-commercial, superiority, stepped wedge cluster randomized controlled trial with a continuous recruitment short exposure design [35]. Individual clusters (i.e. hospital sites) continually recruit patients throughout the trial, initially offering clinic visits according to standard of care and then switching to visits with integrated symptom tracking. Figure 1 shows how a sequence (i.e. pair of sites) switches over in eight steps (i.e. every 3-week period to offer integrated symptom tracking. The order in which sequences switch is randomized (see ‘ Assignment of intervention: allocation and blinding’).

**Fig. 1 Fig1:**
[figure not shown]
Stepped wedge cluster randomized controlled trial design. Healthcare professionals are primarily recruited during an 8-week run-in period (healthcare professional recruitment only; weeks − 8 to 0). All clusters recruit patients for a total of 27 weeks (6.2 months). All sequences initially recruit to clinic visits offering standard of care (control group). In pairs of two (i.e. sequences), clusters are randomly allocated to switch to clinic visits offering integrated symptom tracking (intervention group). All patient participants are followed up for 12 ± 3 months from the time of their allocation

Recruited patients are allocated to receiving either clinic visits with standard of care (i.e. control) or visits with integrated symptom tracking (i.e. intervention) depending on the period in which they are recruited; they continue to receive the clinic visit type they are initially allocated to, including after their cluster has switched over.

Patient participants have at least one baseline and one follow-up visit at 12 months. The final follow-up visit falls within 3 months either side of the 12-month follow-up date to allow for routine outpatient visit scheduling. The rheumatology teams may schedule additional clinic visits during the follow-up period in accordance with usual clinical practice; we will include the data from these additional visits in the analyses.

As part of a hybrid effectiveness-implementation study design [34], we gather information on implementation through the parallel process evaluation. For this, we invite patient participants, healthcare professionals, people involved in implementing integrated symptom tracking, and those eligible but declining trial participation to take part in interviews and/or observations.

### Study setting

This multi-centre trial involves 16 rheumatology outpatient departments (i.e. clusters) providing secondary care for people with RA; supplementary Table S1 contains a list of all participating hospital sites. Sites were eligible as a cluster if they were not yet using integrated symptom tracking as part of their standard of care but had staff who were willing to discuss symptom tracking data with patients as part of clinic visits as well as to collect trial outcome data. Staff members include healthcare professionals, such as rheumatology consultants, registrars and specialist nurses, who are directly responsible for patient care (i.e. conducting patient consultations, assessing disease activity, and/or determining and changing patient management and treatment). Depending on the cluster, these may also include other allied health professionals, such as consultant specialist physiotherapists or specialist pharmacists.

### Interventions

#### Intervention description

##### Integrated symptom tracking (i.e. intervention)

Figure 2 gives an overview of the key elements of the intervention, which we have described in more detail below in line with the Template for Intervention Description and Replication (TIDierR) reporting guidance [36] (see Additional file 2 for completed checklist). Supplementary Figure S1 contains a logic model presenting our hypothesis of how the intervention works.

**Fig. 2 Fig2:**
[figure not shown]
Overview of key element of the integrated symptom tracking intervention. (1) Upon allocation to the intervention group, a patient is ‘prescribed’ integrated symptom tracking through an app they can use on their own smartphone or other mobile device; (2) Using a national user authentication management system (NHS Login), patients securely authenticate themselves; (3) Once authenticated, patients can submit their daily, weekly and monthly data. Prior to the first submission, they are asked to provide electronic consent for reuse of their data for research; (4) Patients’ app data is stored in a regional data repository alongside other, already available clinical data; (5) Healthcare professionals view the app data via an interactive dashboard accessible in clinic within a patient-instance in their electronic health record system

Patients allocated to the intervention group are ‘prescribed’ integrated symptom tracking, i.e. they receive instructions via email on how to set-up, register with, and use an app (i.e. the ‘REMORA app’) on their smartphone or other mobile device to track their symptoms and other patient-reported aspects of living with RA. The instructions also include how to set up or manage a Google account or Apple ID (for downloading the app from the respective app stores), as well as a National Health Service (NHS) login account (to facilitate secure user authentication; see [37]). As part of setting up, they are asked to electronically consent to their app data being used for research. The instruction and all other materials for patient participants are available in the ‘Information for participants’ section on the REMORA website [38].

Once set up, notifications within the REMORA app will prompt daily, weekly and monthly question sets to be completed during the 12 ± 3-month follow-up period; supplementary Table S2 describes the question sets in more detail. Patients receive notifications to remind them to submit their reports. Daily data can be submitted multiple times and at any time of day, with only the final value being viewable during clinic visits. Weekly and monthly questions can only be submitted when prompted. Within the app, patients can visualize and compare their symptom scores over time as graphs. An interactive version of the app is available online [39], with screenshots displayed in Figure S2. Patients have clinic visits in accordance with usual clinical practice and are informed that their tracked symptom data will only be reviewed during these visits and not in-between.

Patient data reported via the app is stored in a regional data repository, from where it is visualized in an interactive REMORA dashboard (see supplementary Fig S3 for screenshots). Consented healthcare professionals receive training [40] prior to trial start on how to use the dashboard for discerning patterns of time-varying disease activity since the patient’s last clinic visit. They can access it from within a patient-instance in their local electronic health record system without needing to log into a separate system. The dashboard consists of two main screens, one visualizing the daily app data, and one visualizing app data submitted weekly and monthly. Healthcare professionals can switch between these options and select any data item to be displayed as a graph for a customizable period. The dashboard is expected to augment rather than replace verbal questions and history taking as part of usual clinical practice but otherwise it is up to healthcare professionals’ discretion how they use the dashboard and discuss the symptom data during clinic visits.

##### Standard of care (i.e. control)

Patient participants allocated to the control group have clinic visits in accordance with usual clinical practice. During these visits, evaluation of how a patient has been since the last appointment is limited to the healthcare professional using verbal questions and history taking as per standard of care. No tracked symptom data is available for review and patients do not have access to the REMORA app. This enables us to evaluate whether the additional effort of implementing integrated symptom tracking into clinical systems and pathways provides benefit compared to hospital outpatient rheumatology services as currently delivered by NHS England.

##### Criteria for discontinuing or modifying allocated interventions

There are no special criteria for discontinuing or modifying allocated interventions. All participants may withdraw from the study at any time, and in addition to a participant formally withdrawing consent, the co-principal investigators can withdraw participants from the study in the event (a) a participant dies, (b) a participant’s capacity to consent changes, or (c) the trial’s sponsor or funder decide to terminate the study (e.g. in the unlikely event of a significant numbers of unanticipated serious safety events, or of sites withdrawing to the extent it invalidates the scientific credibility of the study).

Patient participants not using the intervention as intended are not automatically withdrawn and, unless they formally withdraw, continue to receive requests for data collection. Where a healthcare professional no longer wishes to participate, any consented patient participants under their care are withdrawn with guidance by the study team. If a healthcare professional withdraws because they relocate to another hospital, the colleague taking over their patient list will be approached for REMORA2 trial if not already participating. This will allow consented patients to continue on trial.

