##### Patients participating in the trial

Adult patients (18 years or older) are eligible to take part in the REMORA2 trial if they (a) are under the care of a consented healthcare professional, (b) have active probable/definite RA (see Table S3 for definition), (c) have regular access to an app-compatible, internet-connected mobile device and a valid email address, (d) are able to follow the intervention set-up instructions independently or with support (see ‘ Intervention description’ for details), (e) have a record with clinical data in the regional data repository (see element 4 in Fig. 2) and (f) speak and understand English, or are supported by someone who does.

Patients taking part in the REMORA2 trial can also participate in an interview and/or clinic observation as part of the process evaluation, if they are willing and did not previously participate in the feasibility trial [32].

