##### Electronic health record data extraction

Delegated staff at clusters use an eCRF to enter data extracted from the electronic health record system on clinician-reported disease activity, joint involvement and severity and medication and resource use. For the baseline assessment, this additionally includes patient demographics (gender, date of birth, ethnicity, smoking status, body mass index) and comorbidities.

The baseline assessment is based on information recorded for the clinic visit on, or closest to, the date of recruitment, but within a time window of 6 months prior to or 1 month after consent. Follow-up assessments are performed at each clinic visit during the 12 ± 3-month follow-up window but since these visits are scheduled by the care team as required, no pre-defined schedule of follow-up data extractions has been set.

Healthcare professionals complete paper versions of the eCRFs during follow-up visits to aid data collection.

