### Statistical methods

#### Statistical methods for primary and secondary outcomes

This section summarizes the planned statistical methods for the primary and secondary quantitative outcomes listed in Table 1. For all analyses described below, we will take an intention-to-treat approach, i.e. we will include participants in the treatment group they are assigned to regardless of the extent to which they take up or adhere to the intervention. Further details, including on methods for qualitative outcomes, will be provided in the full statistical analysis plan, which we will draft with input from the trial’s programme steering committee and publish before we lock the trial data set.

We will report the trial results in accordance with the CONSORT stepped wedge trial extension [60].

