#### Methods in analysis to handle protocol non-adherence and any statistical methods to handle missing data

We have developed processes and materials to minimize non-adherence and missing data (see ‘Strategies to improve intervention uptake and adherence (i.e. intervention fidelity)’). Where missing data exists, we will summarize and report missingness in terms of outcome, data source (e.g. eCRF, patient web survey) and reasons for missingness (e.g. participant loss-to-follow-up, withdrawal, protocol deviation).

For the primary outcome analysis, we will use multiple imputation by chained equations where data points are assumed to be missing at random. We will detail multiple imputation model specifications in the full statistical analysis plan, but in general, we will seek to impute across all variables included in the primary and secondary analyses; particularly since we expect the primary outcome (DAS28-CRP) to correlate strongly with other, secondary measures of disease severity (e.g. clinical disease activity index [47]).

A sensitivity analysis will replicate the primary outcome analysis using complete case analysis (i.e. using only observed data from the non-imputed final dataset) and we will present its findings alongside those from the primary outcome analysis. Should the study team feel that data may not be missing not at random (e.g. because of unanticipated events), we will revise the statistical analysis plan to include additional analysis strategies for quantifying the robustness of the point estimate generated from the primary analysis model. Any additional sensitivity analyses will be presented in the main REMORA2 trial report.

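### Patients are withdrawn when their clinician opts out, a rule that weakens intention-to-treat by creating avoidable, clustered and possibly informative missing outcomes

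*Protocol article*

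**What the plan says.** The rule is in the Protocol article, Criteria for discontinuing or modifying allocated interventions: "Where a healthcare professional no longer wishes to participate, any consented patient participants under their care are withdrawn with guidance by the study team". One exception follows. If the clinician leaves because of a move to another hospital, "the colleague taking over their patient list will be approached for REMORA2 trial if not already participating", so that consented patients can stay in the trial.

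The same section treats non-adherent patients differently: "Patient participants not using the intervention as intended are not automatically withdrawn and, unless they formally withdraw, continue to receive requests for data collection". Apart from formal withdrawal of consent, it lists three events that allow the co-principal investigators to withdraw a participant: (a) death, (b) a change in capacity to consent, and (c) termination of the study by sponsor or funder.

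Four other places bear on the point:
- Patients participating in the trial: patients are eligible only if they "are under the care of a consented healthcare professional".
- Statistical methods for primary and secondary outcomes: the analysts will "include participants in the treatment group they are assigned to regardless of the extent to which they take up or adhere to the intervention".
- Electronic health record data extraction: "Delegated staff at clusters use an eCRF to enter data extracted from the electronic health record system". This covers clinician-reported disease activity, and so the primary outcome DAS28-CRP.
- The missing-data section: for the primary outcome, "we will use multiple imputation by chained equations where data points are assumed to be missing at random".

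**The concern.** A consenting patient leaves the trial because a third party stops taking part. Much of that patient's outcome information could still be collected: site staff extract record data, and web surveys go straight to the patient at 3, 6, 9 and 12 months. To that extent the loss is avoidable.

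It is also clustered, since all of one clinician's participants go together. And it may be informative. Clinicians are not blinded, and they join only if willing to review the dashboard, so opting out may reflect their attitude to the intervention or the work it brings.

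Finally, the rule works against the imputation plan. That plan counts on DAS28-CRP correlating strongly with secondary measures of disease severity such as the CDAI, which Table 1 lists as a web-survey outcome. A patient withdrawn at, say, month 4 contributes no later surveys, so the imputation has least to work with where it is most needed.

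**Working it through.** **1. Does the rule end follow-up?** The article does not define withdrawal, but two contrasts within the section point one way. Non-users stay in data collection unless they formally withdraw, so formal withdrawal is what stops data collection. The successor route exists so that patients can remain in the trial, which implies that without it they do not. The natural reading is that follow-up ends. The text does not state whether record extraction stops.

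**2. Does it fit the listed grounds?** A clinician's decision is neither withdrawal of consent by the patient nor any of (a) to (c). The section therefore uses a fourth ground that its own list omits.

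**3. Does it contradict intention-to-treat?** No. The definition concerns analysis by assigned group. Nothing removes these patients from the analysis set, and the missing-data section treats withdrawal as a cause of missing data: it will tabulate "reasons for missingness (e.g. participant loss-to-follow-up, withdrawal, protocol deviation").

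**4. The plan's own sample size (Sample size section).** Recruitment: 27 / [(1 − 0.30)(1 − 0.15)] = 27 / 0.595 = 45.4, rounded up to 46 per site; 46 × 16 = 736. This matches.

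Power uses SD 1.2, difference 0.6, ICC 0.05, cluster autocorrelation 0.8 with discrete time decay, 16 clusters, 8 steps (9 periods) and two-sided 5%. With N = 432, m = 432 / (16 × 9) = 3 per cluster-period. The cluster variance is 0.05 × 1.44 = 0.072. The covariance of a cluster's nine period means is V = 0.072·R + (1.368/m)·I, with R(i,j) = 0.8^|i−j|. Generalised least squares with period effects gives SE = 0.173. Power = Φ(0.6/0.173 − 1.96) = 93.4%, or 89.7% with a t reference on 14 df. A rough allowance for the stated variation in cluster size gives 93.0% and 89.2%. The stated 90% is reproduced within about one point or exceeded.

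**5. Effect of extra loss on power.** The article gives no clinician withdrawal rate, so the extra loss is an assumed range. Each cell gives N analysed, then power (normal / t on 14 df), with the difference held at 0.6.

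| Extra loss | After the plan's full attrition (736 × 0.595) | Non-initiators kept, as intention-to-treat requires (736 × 0.85) |
|---|---|---|
| 0% | 438: 93.7% / 89.9% | 626: 97.9% / 95.7% |
| 5% | 416: 92.8% / 88.8% | 594: 97.5% / 95.1% |
| 10% | 394: 91.7% / 87.5% | 563: 97.0% / 94.3% |
| 20% | 350: 89.2% / 84.4% | 500: 95.6% / 92.5% |

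**6. Block size.** If a site has 3 to 6 consented clinicians (assumed), one withdrawal takes 46/6 = 7.7 to 46/3 = 15.3 participants, or 1.0% to 2.1% of 736.

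**7. Balance between arms.** Sequence 1 switches after 3 of 27 recruitment weeks and sequence 8 after 24. With even accrual (assumed), a clinician's panel is 24/27 = 89% intervention at a sequence 1 site and 3/27 = 11% at a sequence 8 site. Loss concentrated in early- or late-switching sites would therefore be unequal by arm.

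**8. Bias.** Let a fraction f of one arm be lost, and let those patients differ from the retained by d points after covariates and imputation. The true arm mean is (1 − f)·μ + f·(μ + d) = μ + f·d, while the analysis estimates μ, so the bias is f·d in size. For f = 0.05 and d = 0.3 it is 0.015; for f = 0.20 and d = 1.2 it is 0.24. That is 2.5% to 40% of the 0.6 target. Both f and d are assumptions. With loss in both arms, the biases partly cancel if they run in the same direction.

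**The case against.** Five points can be made for the plan.

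- **The rule follows from the design.** Clinicians are trial participants in their own right, dashboard review is part of the intervention, and being under a consented clinician is an eligibility criterion. This explains the rule's origin. But eligibility at entry does not require follow-up to stop later, and intention-to-treat already covers an intervention that is no longer delivered.
- **DAS28-CRP is not independent of the clinician.** The strategies for healthcare professionals include reminders to collect the primary outcome, and clinicians complete paper forms at follow-up visits. Staff can extract only what has been recorded. This stands: continued extraction would recover some primary outcomes, not all. It does not apply to the web surveys.
- **Missing at random may hold.** Site and recruitment date are known for every participant, so loss that depends only on these can be handled. A clinician's panel can also include both arms, so the loss need not be differential. This stands in part. Loss tied to unrecorded features of care would not be covered, and the only missing-data sensitivity analysis fixed in advance is complete-case.
- **The 15% allowance covers drop-out and withdrawal.** It may already include some clinician-driven loss; the article does not say. A reader might infer that the allowance is wrong or that power is in danger. The document does not support either.
- **The article is condensed.** A fuller operational protocol exists and may define what withdrawal entails. That limits confidence, but the rule as printed is explicit.

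A reader might also infer that the plan contradicts its own intention-to-treat principle. It does not, for the reason in step 3 of the working.

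**Conclusion.** The concern holds in a limited form. As written, the rule ends follow-up for consenting patients because of a clinician's decision, fits poorly with the section's own list of grounds and its handling of non-users, and weakens intention-to-treat through missing outcomes that are partly avoidable, clustered and possibly informative. It also removes later patient-reported measures that the imputation would use.

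The size cannot be determined from the document, which gives neither the number of clinicians per site nor their withdrawal rate. Power is not the issue: with 20% extra loss it is 92.5–95.6% if non-initiators are kept, and 84.4–89.2% even after the plan's full attrition. Bias is the issue, with an illustrative range of 0.015–0.24 DAS28 points that rests wholly on assumed inputs. This is a cheap improvement and no ground to doubt the design.

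**What to change.** Amend the section on discontinuing interventions, and the operational protocol if it carries the same rule, as follows:

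1. Separate a clinician's withdrawal from a patient's withdrawal of consent.
2. Unless the patient withdraws consent, continue web surveys and record extraction to the end of the follow-up window, including any DAS28-CRP components recorded in routine care.
3. Analyse these patients in their allocated group.
4. Record clinician-driven events with dates, and report them by arm and site.
5. Reconcile the rule with grounds (a) to (c), so that the list and the text agree.

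These changes concern data collection and reporting only, not care. The cost is a short amendment and a letter to sites, with no added assessments. One limit remains: DAS28-CRP will still be missing where a clinician outside the trial does not record joint counts, but the continued web surveys would then inform its imputation.
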